## Abstract

**Background:**

Total neoadjuvant therapy (TNT) is a preferred method for the treatment of locally advanced rectal cancer (LARC). Two techniques of radiotherapy have been used in TNT trials so far, including long‐course chemoradiotherapy (LCRT) and short‐course radiotherapy (SCRT). However, to date, no study compares these techniques in a head‐to‐head fashion. Our objective is to compare the complete clinical response among patients with LARC who receive long or short‐course radiation therapy in combination with the same chemotherapy regimen.

**Methods:**

158 patients (18–80 years old) with standard or high‐risk LARC (T3/T4 tumor or lymph node positive) located at least 5 cm from the anal verge will be randomized into two groups: LCRT (with a dose of 50.4 Gy in 28 sessions) or SCRT (with a dose of 25 Gy in five sessions). Both of these groups will receive concurrent chemotherapy (capecitabine 825 mg/m^2^ twice daily) followed by consolidation chemotherapy with the CAPEOX regimen for 6 cycles or mFOLFOX7 for 9 cycles. We will compare the complete clinical response (initially 12–16 weeks after the last RT fraction and eventually 2 weeks after the last chemotherapy cycle) by MRI as the primary endpoint. Overall survival (OS), metastasis‐free survival (MFS), local control, and toxicities will be evaluated after 3–5 years as the secondary endpoints.

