## Methods/Design

2

Patients with locally advanced rectal adenocarcinoma (T3 or T4 primary tumor and/or lymph node‐positive disease), who are referred to the Cancer Institute of Imam Khomeini Hospital Complex, Tehran, from September 2023 to the end of March 2025, will participate in this phase 3, randomized, investigator‐blinded, parallel group study. The initial workup comprises total colonoscopy, contrast‐enhanced thoracoabdominopelvic computed tomography (CT) scan, pelvic magnetic resonance imaging (MRI) with intravenous gadolinium, and routine blood tests including tumor markers (carcinoembryonic antigen [CEA] and cancer antigen [CA] 19–9), complete blood count, as well as liver and renal function tests. An expert radiologist will be assigned to review the MRI images and determine the caudal tumor distance from the anal verge, exact T and N staging per the American Joint Committee on Cancer (AJCC) eighth edition, intactness of the mesorectal fascia, circumferential radial margin (CRM), the exact number, location, and the largest size of the pathologic lymph nodes, presence of extramesorectal lymphadenopathies, and extramural vascular invasion (EMVI). For patients who have a high CEA above 20 ng/mL, a positron emission tomography will be requested to rule out distant metastasis. The mismatch repair (MMR) system will be evaluated by immunohistochemistry on the biopsy specimen for all patients before randomization. Informed consent will be obtained from patients after a thorough explanation of the treatment process; if a patient decides to withdraw from the study, they will be removed and receive the standard protocol treatment. The study protocol was approved by the Research Ethics Committees of Imam Khomeini Hospital Complex–Tehran University of Medical Sciences (TUMS) (approval number: IR.TUMS.IKHC.REC.1401.238).

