### Sample Size Calculation

2.7

Considering a predicted cCR rate of 76% as reported in the OPRA trial [18] for the LCRT plus consolidation chemotherapy group, and a cCR rate of 52% in the SCRT plus consolidation chemotherapy as reported by a retrospective study [19], to achieve a 90% power with a two‐sided type I error of 5%, we will require 79 patients in each arm [20]. To compensate for an estimated dropout rate of 20%, we will recruit 95 patients to each study group.

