### Time‐Table

2.8

Patient recruitment duration: 24 months (23/9/2023–22/9/2025).

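### The abstract gives 158, the number required before dropout inflation, as the number to be randomised, while section 2.7 plans 190; the recruitment end date also differs between sections 2 and 2.8

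*Protocol article*

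**What the plan says.** On numbers, the abstract (Methods) has "158 patients (18–80 years old) with standard" or high-risk disease being randomised to the two groups. Section 2.7 builds the sample size from "Considering a predicted cCR rate of 76% as reported in the OPRA trial" for the long-course arm and "a cCR rate of 52% in the SCRT plus consolidation chemotherapy", "to achieve a 90% power with a" two-sided 5% type I error. It arrives at 79 per arm, allows for 20% dropout, and concludes that "we will recruit 95 patients to each study group".

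On dates, section 2 takes patients referred "from September 2023 to the end of March 2025". Section 2.8 has "Patient recruitment duration: 24 months (23/9/2023–22/9/2025").

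Section 2.9 places all analyses in the intention-to-treat population and does not say how patients without a response assessment are counted.

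**The concern.** The number to be randomised and the end of accrual are commitments against which the final report will be read. The article states each of them twice, with different values. For the sample size, 2 × 79 = 158 and 2 × 95 = 190, so the abstract has taken the figure from before the dropout allowance and attached it to randomisation. The difference is 32 patients. Anyone who takes 158 as the target loses the whole allowance that section 2.7 adds for the dropout it expects. For the dates, the two ends of recruitment lie almost six months apart, and both statements are in the body of the article.

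**Working it through.** **Inputs.** From section 2.7: response rates p1 = 0.76 and p2 = 0.52, two-sided alpha 0.05, power 0.90, dropout 20%, 79 required and 95 recruited per arm. From the abstract: 158 randomised. From sections 2 and 2.8: the two end dates.

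**1. Reproduce the plan's figure.** Two proportions, unpooled variance:

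n = (1.960 + 1.2816)² × [p1(1−p1) + p2(1−p2)] / (p1−p2)²
= 10.507 × (0.1824 + 0.2496) / 0.0576
= 10.507 × 0.432 / 0.0576 = 78.8, rounded up to 79.

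This matches exactly. The pooled-variance formula gives 82. The recruitment figure follows from 79 × 1.2 = 94.8, rounded up to 95. So 158 is the number before inflation and 190 the number after it.

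**2. Power if 158 are randomised.** Unpooled: power = Φ(0.24 / √(0.432/n) − 1.96).

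- No dropout, n = 79: 0.24/0.0739 − 1.96 = 1.29, power 90.1% (pooled 88.9%).
- 20% dropout with dropouts excluded, n = 79 × 0.8 = 63.2, so 63: 0.24/0.0828 − 1.96 = 0.94, power about 83% (pooled 81%).

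**3. Power if 190 are randomised.** With 20% dropout excluded, n = 95 × 0.8 = 76, which is 152 in total and not 158: 0.24/0.0754 − 1.96 = 1.22, power 88.9% (pooled 87.7%). The small gap to 90% arises because section 2.7 multiplied by 1.2. Dividing by 0.8 gives 79/0.8 = 98.75, so 99 per arm (198).

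**4. The dates.** From 23 September 2023 to 31 March 2025 is about 18.2 months; to 22 September 2025 it is 24 months. The article gives no accrual rate, so the number reached by the end of March 2025 can only be shown under assumptions:

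| Assumed rate | Source of the rate | Recruited in 18.2 months |
|---|---|---|
| 7.9 per month | 190/24, uniform accrual | about 144 |
| 8.7 per month | 158/18.2 | 158 |
| 10.4 per month | 190/18.2 | 190 |

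**The case against.** Section 2.7 is the dedicated sample-size section and says plainly how many will be recruited. The conflicting figure stands only in the abstract, and its origin is obvious. A reader can therefore identify the intended target, and this stands: it would be too strong to infer that the trial has no identifiable target. It does not make the abstract right, because the abstract calls the 158 randomised, not required or evaluable.

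A reader might also infer that 158 is simply too small for 90% power. The article does not support that. By its own formula 158 fully evaluable patients give 90.1%, and the loss appears only with dropout. That dropout is the plan's own expectation, however, and the only reason why the figure of 95 exists. Nor does the intention-to-treat statement in section 2.9 rescue 158. If dropouts were kept as non-responders (again an assumption), the rates would become 0.76 × 0.8 = 0.608 and 0.52 × 0.8 = 0.416, and pooled power would be about 68% with 158 and 76% with 190.

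A third tempting inference is that the March 2025 date in itself leaves the trial short. An end date has no power of its own. At about 10.4 patients per month the full 190 would be reached by then.

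Finally, one might suspect that two targets in an open-label trial allow the final number to be picked to suit the results. The article describes no interim look, and section 2.6 blinds the radiologist who assesses response and the researcher who analyses the data. The suspicion goes beyond the text.

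**Conclusion.** The concern holds as two unreconciled contradictions in the current text: 158 against 190 randomised, and end of March against 22 September 2025. Neither is a detail that an article leaves to a fuller document, since in both cases two incompatible values are printed.

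The consequence for power is conditional. Randomising 158 would lower it from 90% to about 81–83%, given the assumed 76% and 52%, the plan's 20% dropout, and exclusion of dropouts from the analysis. Without dropout there is essentially no loss. The consequence of the earlier end date cannot be fixed from the article; 144 patients is an illustration under uniform accrual. The 190 in section 2.7 itself falls one to two points short of 90% at 20% dropout. This is minor, but it matters for how the correction is worded.

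**What to change.** - **Abstract:** replace 158 with the number to be randomised under section 2.7, which is 190 as now written. If 158 is kept anywhere, describe it only as the number required before dropout inflation. Do not present it as the evaluable number expected from 190, because 20% dropout leaves 152.
- **Section 2.7:** state the power that 190 gives after 20% dropout: 76 per arm, about 89% by the protocol's formula and 88% pooled. Keeping 79 evaluable per arm at that dropout would take 99 per arm, eight patients more in total. Stating the power as it is requires no extra patients.
- **Sections 2 and 2.8:** give one recruitment period in both.

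The cost is an editorial correction of a few figures, with no change of design and no patients beyond those already planned in section 2.7.

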**Discussion:**

Advances in the treatment of rectal cancer focus on metastasis control, besides local control by using neoadjuvant therapy. Determining the complete clinical response, OS, and MFS of short‐course versus long‐course chemoradiation will assist in choosing the best LARC treatment protocol.

**Trial Registration:**

ClinicalTrials.gov: NCT05920928, 2023.06.27

## Background

1

Locally advanced rectal cancer (LARC) is defined as rectal cancer with positive lymph nodes or T3/T4 primary, without metastasis [1]. Over the past decades, management strategies for LARC have evolved, incorporating a multimodality therapy approach and minimally invasive surgery. Multimodality therapy, which consists of chemotherapy and radiotherapy, is required to reduce the local and distant recurrence rate. Neoadjuvant chemoradiotherapy (CRT), besides the evolved surgical techniques, reduces the local recurrence rate. Until recently, the standard neoadjuvant approach included either a long‐course CRT [2] or a short‐course RT [3]. This preoperative RT or CRT was followed by surgery and adjuvant chemotherapy at the discretion of the treating physician. A successful neoadjuvant treatment could be followed by surveillance, organ preservation, and better quality of life through a watch‐and‐wait approach, rather than radical surgery [4].

Currently, two techniques exist for neoadjuvant radiotherapy: long‐course chemo radiotherapy (LCRT) and short‐course radiotherapy (SCRT) [5]. LCRT involves delivering 50–50.4 Gy of radiotherapy in 25–28 fractions concomitant with 5FU/leucovorin or capecitabine chemotherapy, followed by delayed surgery 8–12 weeks later; meanwhile, SCRT is performed by delivering 25 Gy of radiotherapy in five fractions, usually followed by immediate surgery (during 1 week) [6]. Several studies compared these two methods in terms of cost‐effectiveness, overall survival (OS), disease‐free survival (DFS), treatment compliance, pathologic complete response (pCR), tumor down‐staging, acute toxicity, and sphincter preservation [5, 6, 7, 8].

While neoadjuvant therapy offers substantial benefits compared to surgery alone, it remains constrained by significant limitations. A high rate of distant failure and insufficient local control of high‐risk or low‐lying tumors was the main drawback of conventional neoadjuvant therapies that justified an intensified neoadjuvant approach [9]. The most popular approach has been total neoadjuvant therapy (TNT), which is defined as the delivery of all courses of systemic therapy in the preoperative window before or after RT. TNT enables more effective treatment of distant micrometastases and improves the rate of pCR compared to conventional concurrent CRT [10, 11]. Two pivotal phase III randomized clinical trials compared TNT with standard long‐course CRT in high‐risk rectal cancer. In the PRODIGE‐23 trial [12], the investigational arm received long‐course CRT following chemotherapy, whereas in the RAPIDO trial [13], short‐course RT was followed by chemotherapy. Both trials showed significant benefits in DFS and pCR. Based on the National Comprehensive Cancer Network (NCCN) guidelines [14], both of these approaches at present are considered the standard of care for locally advanced rectal cancer. To date, no head‐to‐head randomized prospective comparisons have directly compared these two TNT approaches. However, the ongoing study by the German Rectal Cancer Study Group (ACO/ARO/AIO‐18.1) [15] is expected to provide valuable insights. We report here the protocol for a randomized clinical trial that aims to compare two schedules of radiotherapy as the main component of TNT with the same concurrent and consolidation chemotherapy regimen regarding the clinical response.

## Methods/Design

2

Patients with locally advanced rectal adenocarcinoma (T3 or T4 primary tumor and/or lymph node‐positive disease), who are referred to the Cancer Institute of Imam Khomeini Hospital Complex, Tehran, from September 2023 to the end of March 2025, will participate in this phase 3, randomized, investigator‐blinded, parallel group study. The initial workup comprises total colonoscopy, contrast‐enhanced thoracoabdominopelvic computed tomography (CT) scan, pelvic magnetic resonance imaging (MRI) with intravenous gadolinium, and routine blood tests including tumor markers (carcinoembryonic antigen [CEA] and cancer antigen [CA] 19–9), complete blood count, as well as liver and renal function tests. An expert radiologist will be assigned to review the MRI images and determine the caudal tumor distance from the anal verge, exact T and N staging per the American Joint Committee on Cancer (AJCC) eighth edition, intactness of the mesorectal fascia, circumferential radial margin (CRM), the exact number, location, and the largest size of the pathologic lymph nodes, presence of extramesorectal lymphadenopathies, and extramural vascular invasion (EMVI). For patients who have a high CEA above 20 ng/mL, a positron emission tomography will be requested to rule out distant metastasis. The mismatch repair (MMR) system will be evaluated by immunohistochemistry on the biopsy specimen for all patients before randomization. Informed consent will be obtained from patients after a thorough explanation of the treatment process; if a patient decides to withdraw from the study, they will be removed and receive the standard protocol treatment. The study protocol was approved by the Research Ethics Committees of Imam Khomeini Hospital Complex–Tehran University of Medical Sciences (TUMS) (approval number: IR.TUMS.IKHC.REC.1401.238).

### Eligibility and Inclusion Criteria

2.1

The eligible patients for participation in this study will be selected based on the following inclusion criteria:
Age between 18 and 80 years oldPatients who have an appropriate performance status (ECOG 0–1 or KPS ≥ 70)Locally advanced adenocarcinoma of the rectum (clinical stage T_3‐4_N_any_ or T_any_N_1‐2_) based on MRI with or without endoscopic ultrasonography (EUS)The epicenter of the tumor should be located below the sacral promontoryThe distal edge of the tumor must be at least 5 cm from the anal verge based on a reliable colonoscopy, digital rectal examination, and MRI.Biopsy‐proven adenocarcinoma

### Exclusion Criteria

2.2

PregnancyHistory of familial syndromes such as familial adenomatous polyposis (FAP) and Lynch syndromeSimultaneous or previous malignancyPatients with a history of previous chemotherapy or radiotherapyTumor recurrence following previous treatmentInability to receive chemotherapy or radiotherapyDistant metastasis detected on chest and abdominopelvic CT and/or positron emission tomography (PET) scansInability to perform MRI due to metal foreign bodies (e.g., prosthetic valve) or claustrophobia

### Treatment Arms 10s

2.3

Long‐course radiation therapy with a dose of 50.4 Gy in 28 fractions along with concurrent chemotherapy with capecitabine at a dose of 825 mg/m^2^ twice daily followed by consolidation chemotherapy with CAPEOX regimen (Capecitabine 1000 mg/m^2^ twice daily for 14 days and intravenous oxaliplatin 130 mg/m^2^ every 3 weeks) for 6 cycles or modified FOLFOX7 regimen (intravenous leucovorin 400 mg/m^2^, infusional 5FU 2400 mg/m^2^, intravenous oxaliplatin 85 mg/m^2^ every 2 weeks) for 9 cycles.Short‐course radiation therapy with a dose of 25 Gy in five fractions, along with concurrent chemotherapy with capecitabine at a dose of 825 mg/m^2^ twice daily in days 1–5, and then consolidation chemotherapy with CAPEOX regimen for 6 cycles or mFOLFOX7 regimen for 9 cycles.

In both arms, the consolidation chemotherapy will begin 2–3 weeks after the last fraction of chemoradiation, when all grade 3 or higher toxicities are resolved (Figure 1).

**FIGURE 1 cam471472-fig-0001:**
[figure not shown]
Study protocol schema.

Upon completion, patients will be offered TME, unless a complete clinical response is observed on restaging with MRI and rectosigmoidoscopy. If a patient has a near‐complete clinical response, then DRE, MRI, and rectosigmoidoscopy will be repeated in 4–8 weeks. In patients with a final complete clinical response, the possibility of a watch‐and‐wait approach will be discussed with the patients if confirmed in a multidisciplinary tumor board. The watch‐and‐wait protocol consists of three‐monthly assessments by CEA and CA19‐9, pelvic MRI with contrast every 6 months, rectosigmoidoscopy every 4–6 months, and thoracoabdominopelvic CT scans annually for 2 years. After that, all the assessments are done on operated patients up to 5 years.

### Endpoints

2.4

#### Primary Endpoint

2.4.1

Complete clinical response (cCR) will initially be assessed by MRI and rectosigmoidoscopy 12–16 weeks following the termination of radiotherapy. A second assessment will be done 2 weeks after all chemotherapy cycles are given (22–23 weeks post‐RT) using digital rectal examination, rectosigmoidoscopy, and MRI. The MRI report must indicate the regression of the tumor and the extent of residual tumor signal on T2 and diffusion‐weighted imaging (DWI) sequences (mrTRG: 1–5 [16]), and rectosigmoidoscopy must show a complete response to therapy (including normal, whitish scar and/or telangiectasia without any ulcer or polypoid tissue or a mass and stenosis [17]). Patients with either a reliable mrTRG score of 4 or 5 at the first assessment will be referred for surgery if they are M0 in re‐staging. Using a PET scan is optional for further evaluation in suspected cases.

#### Secondary Endpoints

2.4.2

Following the completion of treatment, patients will be monitored, and the rates of local, regional, and distant failure will be recorded in 3 and 5 years, respectively. Local recurrence‐free survival, regional recurrence‐free survival, distant metastasis‐free survival, and OS will be evaluated as secondary endpoints, with the last chemotherapy cycle date being the reference time point for survival outcome calculation. We will also perform a subgroup analysis on an MRI‐defined high‐risk group with either of the following features: elevated CEA (> 20 ng/mL), cT4, cN2, positive CRM, presence of EMVI, pathologic extramesorectal lymphadenopathies, and/or large (short axis diameter ≥ 1 cm) mesorectal lymph nodes. Treatment‐related adverse events, including gastrointestinal, genitourinary, hematologic, and skin toxicities, will be graded using the Common Terminology Criteria for Adverse Events (CTCAE) version 5 and compared between the two treatment arms. Throughout the study period, patients will undergo periodic blood tests and physical examinations.

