### Statistical Analysis

2.9

Basic descriptive tests will be used for qualitative data. Normality will be tested for the quantitative data using the Kolmogorov–Smirnov test. To compare the qualitative data, Pearson's chi‐squared test, and for the comparison of quantitative data, an independent samples t‐test will be used. A binary logistic regression analysis will be performed to determine the predictors of cCR. All analyses will be done in the intention‐to‐treat population. We will also perform subgroup analysis on patients with a cCR who choose a watch‐and‐wait approach after TNT to determine predictors of survival outcomes. Analyses will be done using IBM SPSS Statistics version 26 with a *p* value of 0.05 as the significance boundary.

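### Survival endpoints are timed from the last chemotherapy cycle, a post-randomisation date that varies with arm and tolerance and conflicts with the stated intention-to-treat analysis

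*Protocol article*

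**What the plan says.** Section 2.4.2 (Secondary Endpoints) lists local recurrence-free, regional recurrence-free, distant metastasis-free and overall survival, "with the last chemotherapy cycle date being the reference time point for survival outcome calculation". The same section places follow-up after treatment: "Following the completion of treatment, patients will be monitored". No section gives randomisation as the origin for any of these endpoints.

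Section 2.9 (Statistical Analysis) states: "All analyses will be done in the intention‐to‐treat population".

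Three other statements determine when the last cycle falls:

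- Section 2.3 gives one arm radiotherapy "with a dose of 50.4 Gy in 28 fractions" and the other "with a dose of 25 Gy in five fractions".
- Section 2.3 also says that "the consolidation chemotherapy will begin 2–3 weeks after the last fraction of chemoradiation, when all grade 3 or higher toxicities are resolved".
- Section 2.4.1 says: "Patients with either a reliable mrTRG score of 4 or 5 at the first assessment will be referred for surgery", provided that restaging shows no metastases. That assessment is 12–16 weeks after radiotherapy.

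**The concern.** In a randomised comparison the clock should start at a date that treatment cannot influence. The date of the last chemotherapy cycle does not qualify. It moves with the length of radiotherapy, which differs by arm, and with toxicity, which can delay, shorten or prevent consolidation. It may also move with response.

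This has two consequences. Some patients have an event before their time zero, or have no time zero, yet an intention-to-treat analysis must include them. The remaining patients are compared over windows that do not begin at the same point after randomisation.

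The effects do not all push the same way. For the same event date after randomisation, a long-course completer is credited with a shorter time than a short-course completer. On the other hand, the longer uncounted window in the long-course arm can hide more early failures. The net direction cannot be predicted, so it cannot be allowed for when the results are read.

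**Working it through.** **Inputs from the document.** Radiotherapy of 28 or 5 fractions; a gap of 2–3 weeks to consolidation; CAPEOX for six 3-week cycles or mFOLFOX7 for nine 2-week cycles (all section 2.3). Second assessment two weeks after chemotherapy, stated as 22–23 weeks after radiotherapy (section 2.4.1). 95 patients per arm (section 2.7).

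**Assumptions not in the document.** Five fractions per week without breaks; radiotherapy starting close to randomisation; the cycle date read as day 1 of the cycle; treatment on schedule.

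**1. Reproduce the plan's own figure.** Both regimens last 18 weeks (6 × 3 and 9 × 2). Gap + chemotherapy + 2 weeks gives 2 + 18 + 2 = 22 and 3 + 18 + 2 = 23. This matches the stated 22–23 weeks, so the schedule has been read correctly.

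**2. Day 1 of the last cycle, in weeks after radiotherapy.**

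- CAPEOX: gap + 5 × 3 = 17–18
- mFOLFOX7: gap + 8 × 2 = 18–19

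**3. Add the length of radiotherapy, by arm.**

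| Count | Short course | Long course | Difference |
|---|---|---|---|
| Fractions ÷ 5 | 1.0 week, so time zero at 18–20 | 5.6 weeks, so time zero at 22.6–24.6 | 4.6 weeks |
| First to last fraction, Monday start | 4 days, so 17.6–19.6 | 37 days, so 22.3–24.3 | 33 days, or 4.7 weeks |

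Either way, about 4 to 6 months after the start of radiotherapy are not counted, and time zero is about 4.6 weeks later in the long-course arm for the same regimen and gap.

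**4. Tolerance.** Stopping after cycle 1 rather than completing moves time zero earlier by 5 × 3 = 15 weeks (CAPEOX) or 8 × 2 = 16 weeks (mFOLFOX7). This is more than three times the scheduled difference between arms. Waiting for toxicity to resolve before consolidation moves it later.

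**5. Response (conditional).** Suppose chemotherapy stops when a patient is referred for surgery at 12–16 weeks after radiotherapy, and a cycle due that week is still given. The last cycle is then 3–6 weeks earlier than a completer's under CAPEOX and 2–8 weeks earlier under mFOLFOX7. Section 2.7 plans on response rates of 76% and 52%, so if chemotherapy did stop, the shift would probably be unequal between arms.

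**6. What the rule does to each kind of patient.**

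- Recurrence or metastasis found before the last cycle, for example at the first restaging with chemotherapy continuing: negative time.
- No consolidation given: no clear time zero, because the text does not say whether concurrent capecitabine counts as a cycle.
- Death during consolidation: this follows the patient's own last cycle, so it is counted, with a very short time.
- Completion on schedule: valid time, but from a different point in each arm.

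**7. Illustration of scale.** The document gives no early event rate. Assume a constant hazard and 3-year event-free survival of 75–90%. With λ = −ln(S) ÷ 156 per week, the proportion with an event before week w is 1 − exp(−λw). For S = 0.75 and w = 24.3 this is 4.4%, or 4.2 of 95. Across the range, about 1–3 short-course and 1–4 long-course patients per 95 have an event before the scheduled time zero. Under these assumptions the number with a negative or undefined time is smaller, because deaths during consolidation remain in the analysis.

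**The case against.** The strongest defence is that the effect is modest and confined to secondary endpoints. A shift of 4.6 weeks is about 1.8–2.9% of 3–5 years (4.6 ÷ 260 and 4.6 ÷ 156). Under constant hazards, a shifted origin leaves the hazard ratio among patients still at risk unchanged. The primary endpoint is scheduled separately, and the sample size rests on clinical response alone. All of this stands, and it limits the weight of the point. It does not answer the undefined or negative times, or the much larger shifts for patients who stop early.

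Several stronger readings are tempting, but the document does not support them:

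- **All early events are lost.** Deaths during consolidation are still counted. Only recurrences or metastases before the last cycle, and patients with no chemotherapy date, are affected in that way.
- **Survival will be compared by chi-squared or t-test.** Section 2.9 assigns those tests to qualitative and quantitative data and names no between-arm survival method. In a condensed article that is silence, not an error.
- **Surgical referral ends consolidation.** Section 2.4.1 does not say so, and dependence on response is therefore conditional.
- **The survival comparison is no longer randomised.** The text does not say that patients without a time zero will be dropped. The origin conflicts with intention to treat, but how far the comparison is damaged depends on how such patients are handled.

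**Conclusion.** The point holds in a limited form. The time origin is stated explicitly, nothing else in the document overrides it, and it conflicts with the intention-to-treat statement in section 2.9.

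The scheduled difference between arms is about 4.6 weeks, given five fractions per week and treatment on schedule. Differences between patients within an arm can reach 15–16 weeks when treatment stops after the first cycle. The number of patients with a negative or undefined time cannot be derived from the document. The illustration suggests a handful per arm at most, and it rests on assumed event rates. With 95 patients per arm, a few misplaced events can still matter to a survival comparison.

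This should be fixed, but it does not put the trial's main conclusion at risk: the primary endpoint and the sample size are unaffected.

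**What to change.** Amend the sentence in section 2.4.2 along these lines: all time-to-event endpoints are measured from the date of randomisation, in all randomised patients, analysed by allocated arm; an event found before chemotherapy ends counts on the date it is found. If the last-chemotherapy origin is of clinical interest, keep it only as a labelled descriptive landmark analysis.

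The cost is one sentence. No treatment, visit or sample-size change is needed. The date of randomisation must be held for every patient; section 2.5 allocates by time of enrolment, which implies that a date exists but does not say so, and this should be confirmed. The change is best made before follow-up matures, so that the choice of origin cannot be influenced by the results.

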### Blinding

2.6

Blinding will only be applied at the level of treatment response assessment by a radiologist who will be blinded to the treatment groups, as well as the researcher in charge of data analysis. The treatment nature does not allow blinding of the patients and the physicians in charge of treatment.

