No study has yet prospectively compared SCRT and LCRT, both given with TNT protocols, and this was the rationale for us to design the current study in which we will be comparing the efficacy and toxicities of both SCRT and LCRT, followed by consolidation chemotherapy to determine the best TNT strategy for rectal cancer patients. Due to the present concerns about the re‐growth rate in SCRT patients who achieve a clinical complete response in a report from the Memorial Sloan‐Kettering Cancer Center [30], and the concerning rate of local recurrence in the updated long‐term analysis of the RAPIDO trial [23] we will not be recruiting low‐lying tumors as an extra precaution measure until more convincing evidence is available regarding the noninferiority of SCRT compared with LCRT for organ preservation. A similar study is also being conducted in Germany (ACO/ARO/AIO‐18.1, NCT04246684) [15] with a primary endpoint of 3‐year organ preservation rate and an estimated completion date of 2028.

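### The between-arm safety comparison rests on treatment-related adverse events in a trial with unblinded treating physicians; an all-cause comparison would be less open to attribution bias (minor)

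*Protocol article*

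**What the plan says.** Section 2.4.2 (Secondary Endpoints) states: "Treatment‐related adverse events, including gastrointestinal, genitourinary, hematologic, and skin toxicities, will be graded using the Common Terminology Criteria for Adverse Events", version 5, "and compared between the two treatment arms". This is the only between-arm safety comparison that the article defines. On data collection the same section adds: "Throughout the study period, patients will undergo periodic blood tests and physical examinations". It names no assessor of relatedness and no attribution rule.

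Section 2.6 (Blinding) states: "Blinding will only be applied at the level of treatment response assessment by a radiologist who will be blinded to the treatment groups". It extends blinding to the researcher who analyses the data, and then says: "The treatment nature does not allow blinding of the patients and the physicians in charge of treatment".

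Toxicity is a named secondary endpoint. The abstract says that "local control, and toxicities will be evaluated after 3–5 years as the secondary endpoints", and the Discussion gives comparison of the toxicities of the two schedules as part of the trial's purpose.

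**The concern.** Randomisation balances the occurrence of adverse events from all causes, apart from any effect of treatment. It does not balance a judgement made after randomisation by someone who knows the arm. If an event enters the comparison only once it is called treatment-related, the counted rate in each arm is the true rate multiplied by that arm's probability of attribution. A gap between the two probabilities shows up as a toxicity difference, or offsets a real one.

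The tumour stays in place throughout neoadjuvant treatment, so bleeding, bowel symptoms, pain and anaemia can plausibly be put down to either disease or treatment. Neither safeguard in the article acts at this step. CTCAE standardises severity, not cause, and the blinded analyst receives events that have already been classified. At stake is the credibility of the safety half of the comparison between schedules, not the primary endpoint.

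**Working it through.** **Inputs from the article.** Section 2.7 gives 79 patients required per arm and 95 recruited per arm. It gives no toxicity rate and no attribution rate.

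**The article's own figure first.** Section 2.7 starts from "Considering a predicted cCR rate of 76% as reported in the OPRA trial" for the long-course arm and 52% for the short-course arm, with 90% power and a two-sided 5% error. With unpooled variance:

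n = (1.960 + 1.282)² × (0.76×0.24 + 0.52×0.48) / 0.24² = 78.8, so 79 per arm.

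This reproduces, and 79 × 1.2 = 94.8 gives the 95. These figures serve here only as arm sizes.

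**Assumptions, not in the article.** The all-cause event rate p is equal in both arms, at 30%, 40% or 50%. The probabilities that an event is called related, a₁ and a₂, are 95% against 90%, 90% against 80%, or 90% against 70%.

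**Formula.** Counted rates are p₁ = p·a₁ and p₂ = p·a₂, with d = p₁ − p₂. Let se₀ be the pooled and se₁ the unpooled standard error of the difference. The two-sided rejection probability is

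Φ[(d − 1.96·se₀)/se₁] + Φ[(−d − 1.96·se₀)/se₁].

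**One case in full** (p = 40%, 90% against 80%, n = 95): p₁ = 0.36, p₂ = 0.32, d = 0.04, se₀ ≈ se₁ ≈ 0.0687. The terms are Φ(−1.38) = 0.084 and Φ(−2.54) = 0.0055, which sum to 8.9%.

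**All cases** (ranges run over p = 30% to 50%):

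| Attribution | Spurious difference | Rejection, 95 per arm | Rejection, 79 per arm |
|---|---|---|---|
| 95% vs 90% | 1.5–2.5 points | 5.6–6.4% | 5.5–6.1% |
| 90% vs 80% | 3–5 points | 7.6–10.7% | 7.2–9.7% |
| 90% vs 70% | 6–10 points | 16.2–28.9% | 14.2–24.9% |

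**Masking.** Suppose true all-cause rates of 45% and 25%. Compared directly, the power is about 83% at 95 per arm (76% at 79). With 70% attribution in the first arm and 90% in the second, the counted rates are 0.45×0.70 = 31.5% and 0.25×0.90 = 22.5%. The difference falls from 20 points to 9, and the power to about 29% (25% at 79). This uses the same extreme attribution gap, so it shows that the bias can run in both directions, not how large it is likely to be.

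**The case against.** The other side has several good points.

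- **Two links are inferred.** The article does not say that unrelated events go unrecorded or uncompared, nor who judges relatedness. A condensed article commonly leaves collection and attribution rules to the full protocol. This stands as a limit: a reader might infer that treating physicians filter events one by one, but the text does not say so. What remains is that the article itself fixes the compared set as treatment-related events and assigns the judgement to neither blinded role.
- **Shared drugs.** Both arms receive pelvic radiotherapy, concurrent capecitabine and the same consolidation options, and treatment-related is not restricted to radiotherapy. Many events may be called related in both arms, and haematologic events are laboratory values. This stands, and it makes a gap of 90% against 70% extreme.
- **Surgical morbidity.** TME depends on response, and section 2.7 plans on 76% against 52%. All-cause counting with no end date would mix in surgical events expected to differ by arm. This also stands, and the fix needs a bounded window.

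Two stronger readings are tempting and are not supported. A reader might take the Discussion's caution, "as an extra precaution measure until more convincing evidence is available regarding the noninferiority of SCRT compared with LCRT for organ preservation", as evidence of a prior belief that would bias attribution. That passage concerns regrowth, local recurrence and organ preservation, and explains why low-lying tumours are not recruited. It states no belief about toxicity. A reader might also point to 28 radiotherapy sessions against 5. More contact affects how many events are noticed, which is a detection issue that an all-cause count shares.

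**Conclusion.** The point holds in a modest form. Making treatment-related events the compared set, with treating physicians unblinded, opens a route for attribution bias that the article's safeguards do not close. Neither direction nor size can be derived from the document. On the assumed rates, the false-positive probability with 95 per arm goes from 5% to about 6% under a small attribution gap and to 8–11% under a moderate one. It reaches 16–29% only under an extreme gap. If nearly every event is called related in both arms, the bias is negligible, but then restricting the comparison gains nothing either. One secondary endpoint is affected; the primary endpoint and the sample size are not.

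**What to change.** In section 2.4.2, make the main between-arm safety comparison all adverse events regardless of attribution, for any grade and for grade 3 or higher, by CTCAE version 5. Run it from the start of radiotherapy to the end-of-treatment response assessment or TME, whichever comes first. Tabulate later and surgical events separately by arm, and keep the treatment-related subset as a supportive table.

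The cost is one or two sentences, slightly more event recording, and some dilution by disease-related events. No sample size or treatment rule changes. Recording should be settled early, because unrelated events that were never collected cannot be recovered. Three limitations remain and should be stated: grading and symptom reporting are still unblinded, visit contact is unequal, and the window differs in length between patients (longer with more radiotherapy sessions, shorter for those who go to surgery early). Reporting the observation time by arm beside the event table would let readers judge the last of these.
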